###### **c. Non-inclusion criteria**

- Congenital malformations which may affect psychomotor development;
- History of neurological pathologies with impact on psychomotor development;
- Any child of drug addicted mothers.

### 3.1.3. Expected results

- **Prevalence of psychomotor developmental delay:** assess the skills and abilities acquired in each of the 4 domains of DPM (Motor skills, language, cognition and sociability);
- **Evolution of psychomotor development according to the dose of RUTF received:** compare the improvement in the acquisition of skills and abilities acquired in each of 4 areas of DPM according to the dose of RUTF received according to the trial protocol.

### 3.1.4. Sample size

$$n = t^2 \times p \times (1-p) / m^2$$

- *n: Minimum sample size to obtain significant results for an event and a fixed level of risk*
- *t: Confidence level (the typical value of the 95% confidence level will be 1.96)*
- *p: estimated proportion of the population exhibiting the characteristic studied (0.50 is considered if p is unknown);*
- *m: Margin of error (generally set at 5%).*

Applying the above formula, the minimum sample for this study is 384 children. After rounding up, a total of 400 children will be included in the study on psychomotor development, including 200 in the intervention group (reduced dose) and 200 in the control group (standard dose).

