### **Secondary assumptions**

- Children receiving the reduced dose of RUTF will have the same performance indicators (cure rate, death, drop-out, relapse) as those receiving the standard dose;
- Children receiving the reduced dose of RUTF will have the same length of stay as those receiving the standard dose;
- Children receiving the reduced dose of RUTF will have the same psychomotor development as those receiving the standard dose;
- Treatment with a reduced dosage of RUTF will be less expensive than treatment with the standard dose.

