### **2.3.3. Statistical analyzes**

For the quantitative part of the study, the data will be summarized in Mean and Standard Deviation if they are normally distributed (normality test) for continuous variables and in absolute and relative frequencies for categorical variables.

The t-test and the chi-square test will be used respectively to compare the means and the proportions of the socio-demographic characteristics at admission for the quantitative and qualitative variables.

Linear regression analyzes will be used to determine the significant differences between the 2 groups of children for the quantitative variables.

Binary logistic regression analyzes will be used to determine the significant differences between the 2 groups of children for the binomial qualitative variables (2 response modalities).

Multinomial logistic regression analyzes will be used to determine the significant differences between the 2 groups of children for the multinomial qualitative variables (3 or more modalities).

All analyzes will be done in an adjusted and unadjusted model and a difference is statistically significant when the P-value is less than 0.05.

The results will be analyzed using statistical software, in this case STATA, version 17.

The main analyzes will be done by intention to treat (ITT) and per protocol for the main result, in this case, the speed of weight gain. The other secondary results will be analyzed only by intention to treat (ITT).

For the DPM, a score will be assigned to the participant and the sum will constitute the total score for each participant per domain.

For focus group data, after transcription of the recordings into Word 2019, thematic analysis will be done using Excel tables (matrix) or Nvivo® software.

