## **2. Goals**

a. Main objective

Contribute to improving the overall care of children with SAM without medical complications by integrating aspects of psychomotor development.

b. Specific objectives

The specific objectives of this study are:

- To determine the prevalence of RDPM in SAM children without medical complications in the ZS of Nzaba and Bonzola in the province of Kasai Oriental in the DRC;
- Evaluate the evolution of psychomotor development in SAM children without medical complications in the ZS of Nzaba and Bonzola in the province of Kasai Oriental in the DRC;

To compare psychomotor development in SAM children without medical complications as a function of the dose of RUTF received in the ZS of Nzaba and Bonzola in the province of Kasai Oriental in the DRC.

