### **3.3.2. Data analysis**

Descriptive analysis (percentage, medians with interquartile space and extremes, means plus or minus standard deviation) will be performed for categorical data.

The chi-square test will be used for the comparison of proportions and the Student's t-test to compare the means in the two groups.

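### The psychomotor sub-study's 400 children come from a one-group prevalence formula that gives no basis for the comparison of arms, and its difference tests cannot show that development is the same in both arms

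*Protocol*

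**What the plan says.** - **Hypothesis.** Under Research hypotheses, Secondary assumptions, the protocol expects that "Children receiving the reduced dose of RUTF will have the same psychomotor development as those receiving the standard dose".
- **Objective.** Annex 3, section 2 (Goals) lists the prevalence of developmental delay, its evolution, and a third aim: "To compare psychomotor development in SAM children without medical complications as a function of the dose of RUTF received". Section 3.1.3 of the annex repeats the comparison by dose as an expected result.
- **Size.** Annex 3, section 3.1.4 applies a single-proportion formula and describes n as the "Minimum sample size to obtain significant results for an event and a fixed level of risk". For t, "the typical value of the 95% confidence level will be 1.96"; for p, "0.50 is considered if p is unknown"; the margin of error m is 5%. The result is 384, rounded up to 400, with 200 per arm.
- **Tests.** Annex 3, section 3.3.2: "The chi-square test will be used for the comparison of proportions and the Student's t-test to compare the means in the two groups". Section 2.3.3 of the main text adds adjusted and unadjusted regression models and the rule that "a difference is statistically significant when the P-value is less than 0.05".
- **Margin.** The protocol's only non-inferiority margin is for weight gain. Psychomotor development has none.

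**The concern.** The sample size, the hypothesis and the tests are all fixed in the protocol, and they answer different questions. The formula asks how precisely one prevalence can be estimated in one group. The hypothesis asks whether two arms are alike. The tests ask whether two arms differ.

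The text presents the size as enough for significant results and then divides it by arm, which invites the belief that the comparison has been sized. Development is an outcome on which harm from less RUTF could appear. If the chi-square test gives P above 0.05, that result would seem to confirm the hypothesis, although the interval around the difference might still contain a considerable excess of delay.

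**Working it through.** **Inputs.** From Annex 3, section 3.1.4: t = 1.96, p = 0.50, m = 0.05, 200 per arm. From section 2.3.3: significance level 0.05; sidedness is not stated, so two-sided is taken. Assumed here, because the protocol names no between-arm difference: a 10-point excess of delay, over a range of control prevalences. Also assumed: 150 per arm reassessed at discharge. Section 2.3.1 f limits the end-of-treatment assessment to children declared cured, Annex 4 says outpatient cure often exceeds 75%, and 0.75 × 200 = 150.

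**1. The plan's figure.** 1.96² × 0.50 × 0.50 / 0.05² = 384.16. The stated 384 reproduces.

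**2. What 400 delivers for one pooled prevalence.** 1.96 × √(0.25/400) = 0.049, or 4.9 points, as intended.

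**3. What it delivers for the arm difference.** Half-width = 1.96 × √(2p(1−p)/n per arm).
- p = 0.50, n = 200: 1.96 × √(0.5/200) = 0.098, or 9.8 points.
- p = 0.50, n = 150: 1.96 × √(0.5/150) = 0.113, or 11.3 points.
- p = 0.20, n = 200: 7.8 points. p = 0.10, n = 200: 5.9 points.

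**4. Power for an illustrative 10-point excess.** Power = Φ{[Δ − 1.96√(2p̄(1−p̄)/n)] / √([p₁(1−p₁) + p₂(1−p₂)]/n)}. For 50 v 60% with n = 200: (0.10 − 1.96 × 0.04975)/0.04950 = 0.050, and Φ(0.050) = 0.52.

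| Delay, control v reduced dose | Power, 200 per arm | Missed, 200 per arm | Missed, 150 per arm (exact enumeration) |
|---|---|---|---|
| 50 v 60% | 52.0% | 48% | 57% |
| 30 v 40% | 55.5% | 44% | 56% |
| 20 v 30% | 63.8% | 36% | 48% |
| 10 v 20% | 80.2% | 20% | 31% |
| 5 v 15% | 91.8% | 8% | 16% |

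Exact enumeration at 200 per arm gives 48, 44, 36, 19 and 7% missed, so the approximation is sound there. At 150 per arm and 50 v 60% the approximation gives 59% missed, against the exact 57%.

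**5. Mean scores.** Power ≈ Φ(d√(n/2) − 1.96), with d in SD units. At 200 per arm: 0.2 SD 51%, 0.3 SD 85%, 0.5 SD over 99%. At 150 per arm, 0.3 SD has 74%.

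**The case against.** **The formula is right for one objective.** Prevalence of delay is the sub-study's first specific aim, and 384 is a correct size for it. This stands. The gap concerns only the comparison by dose.

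**A reader might infer that a 10-point excess is missed about half the time, whatever the setting.** The documents do not support this. The 0.50 is a default for an unknown prevalence, not an expected rate, and the 10 points are not in the protocol. The miss rate falls to about 20% at 10 v 20% and 8% at 5 v 15%. The only prevalences that Annex 3 cites, 4.1 and 4.9 (read as percentages), lie at that low end. They concern severe retardation and are not stated to be for children with SAM, so they do not replace 0.50 either.

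**A reader might also infer that the protocol says a non-significant test will be reported as sameness, or that it attaches its 5% to the arm difference.** It says neither. It states a hypothesis of sameness, gives only difference tests, and leaves open what a non-significant result would mean.

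**The regression models could do better than the t-test.** Section 2.3.3 allows adjusted models, and development is measured at admission. With an assumed correlation of 0.6 between admission and later score, the residual SD shrinks by √(1 − 0.36) = 0.8. A 0.2 SD difference then acts like 0.25 SD, and power at 200 per arm rises from 51% to about 70%. This is a fair point on power. It supplies no margin and does not turn a difference test into evidence of sameness.

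**Interpretation of secondary outcomes often belongs in the SAP.** That is true of reporting detail. But the protocol itself fixes the size, its justification, the hypothesis and the tests, and a later plan cannot make a one-group formula justify a two-group comparison.

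**Conclusion.** The concern holds in a bounded form. The 400 children give about 5-point precision for the pooled admission prevalence and nothing designed for the comparison of arms. At the protocol's default p = 0.50, the arm difference is known only to within 9.8 points if all 200 per arm are reassessed, and 11.3 points with 150. Miss rates for a 10-point excess run from 48% (50 v 60%) to 8% (5 v 15%) at 200 per arm. They are illustrations that depend on an assumed difference and an unknown prevalence.

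The structural conclusion needs neither assumption: with no margin, P above 0.05 does not show that development is the same, at any prevalence. Because this is a secondary outcome in a nested sub-study, the point deserves correction but does not threaten the trial's main result.

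**What to change.** - **Annex 3, section 3.1.4.** Say that 5-point precision applies to the pooled admission prevalence only. Drop the reference to significant results as a reason for the arm comparison. State that the arm difference has about 9.8-point precision at p = 0.50 with all 200 per arm reassessed, and about 11.3 points with 150.
- **Secondary assumptions, and Annex 3, section 3.3.2.** Report the arm difference with its 95% confidence interval, for delay and for the domain scores. State that P above 0.05 will not be read as sameness.
- **Any claim of not worse.** Make it only if the interval excludes a margin that the sponsor fixes and justifies before the data are seen. Otherwise call the comparison exploratory. The choice of margin, and whether delay or domain scores lead, are design decisions for the sponsor.
- **Any power quoted for mean scores.** Give it for the number expected to be reassessed: for 0.3 SD, 85% at 200 per arm but about 74% at 150.

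**Cost.** No extra children or visits. The stated precision becomes less favourable and the claim narrower.

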#### **2.1.5.Places of inclusion of children**

A total of 14 UNTAs will be selected for this study due to 7 UNTAs per health zone. The UNTA selection criteria are as follows:

- Have a good attendance: the selection will start from the most frequented UNTAs to the less frequented;
- Be geographically accessible;
- Be covered by a telephone network.

The table in appendix 6 shows the elements of the UNTA typology including the average monthly attendance, the percentage of malnourished children admitted per month, the number of population served by the health area, the number of trained staff in post, the number of days disruption of inputs (average per month), the days of PCIMA activity.

Chart 7 : Health areas selected for the study

| Bonzola health zone | Nzaba health zone |
|---------------------|-------------------|
| 1 Mudiba            | 8 Of the market   |
| 2 Solola            | 9 Tudikolela      |
| 3 Tubondo 2         | 10 PMKO           |
| 4 Dubai             | 11 Lutulu         |
| 5 Kashala Bonzola   | 12 Airport        |
| 6 Nyongolo          | 13 Tarmac 2       |
| 7 Lubilanji         | 14 Tatu muya      |

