##### **b. Data collection plan**

##### ***Staff recruitment and training***

The study must be organized in conditions as close as possible to road practice. As a result, the providers assigned to taking anthropometric measurements will also be responsible for evaluating the psychomotor development of each participant.

These providers will be trained by the psychomotor therapist in order to become familiar with the use of ASQ3 and the assessment of the psychomotor development of the participants.

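### The psychomotor sub-study's 5-point margin rests on a simple-random-sample formula, but the children come from 14 purposively chosen centres that do their own testing, so the margin is not secured

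*Protocol*

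**What the plan says.** All references are to the protocol.

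- **Objective.** The first specific objective of the sub-study (Annex 3, section 2) is "To determine the prevalence of RDPM in SAM children without medical complications in the ZS of Nzaba and Bonzola". The target is therefore the two zones, not a list of centres.
- **Sample size.** Annex 3, section 3.1.4 uses n = t² p(1−p)/m², with t = 1.96, p = 0.50 as the default for an unknown proportion, and m = 5%. It concludes: "Applying the above formula, the minimum sample for this study is 384 children". The figure is then raised to 400, with 200 in each arm. No design effect, ICC or centre term enters.
- **Centres.** Section 2.1.5: "A total of 14 UNTAs will be selected for this study due to 7 UNTAs per health zone". They are chosen by attendance (busiest first), geographic access and telephone coverage. Section 2.1.1 counts 15 health centres in Bonzola and 18 in Nzaba, and says that 2 and 5 of the UNTAs respectively are not functional.
- **Children within centres.** Selection is systematic (Annex 3, 3.1.5) and allocated to the UNTAs by demographic weight (Annex 3, 3.2).
- **Testers.** Annex 3, 3.3.1 b: "the providers assigned to taking anthropometric measurements will also be responsible for evaluating the psychomotor development of each participant". The staffing paragraph of main section 2.3.1 b puts two such providers in each UNTA.
- **Analysis.** Annex 3, 3.3.2 names descriptive statistics, the chi-square test and the t-test.

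**The concern.** The formula gives a 5-point margin only if the 400 results behave like 400 independent draws from the SAM children of the two zones. Two features of the plan work against this. Children at one centre share a catchment area, so true rates of delay may differ between centres. They are also scored by the same one or two local providers, so a strict or lenient tester shifts a whole centre together. Both make results within a centre alike and reduce the information in 400 children. Systematic selection inside each centre does not remove either effect.

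The prevalence is the first objective of the sub-study and the only quantity for which its sample size was derived. If the margin is carried into the report as stated, or the interval is computed as for independent children, the precision claimed for the two zones may be better than the design gives.

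**Working it through.** **Inputs from the protocol.** t = 1.96, p = 0.50, m = 0.05, n = 400 (Annex 3, 3.1.4); 14 UNTAs, 7 per zone (2.1.5); 15 + 18 = 33 health centres, with 2 + 5 = 7 UNTAs not functional (2.1.1). Reading 2.1.1 as one UNTA per health centre leaves 33 − 7 = 26 functional UNTAs.

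**Assumed input.** The protocol gives no ICC. It is shown at 0.02, 0.05 and 0.10.

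**1. The plan's own figure.** 1.96² × 0.25 / 0.05² = 384.16, so 384 is reproduced. With 400 independent children the half-width is 1.96 × √(0.25/400) = 4.9 points.

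**2. The slack.** The margin stays at 5 points while the design effect is at most 400 / 384.16 = 1.041. The mean cluster size is 400/14 = 28.6, and the design effect is 1 + (28.6 − 1) × ICC. The largest tolerable ICC at p = 0.50 is 0.041 / 27.6 = 0.0015.

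**3. Half-width under clustering.** Half-width = 1.96 × √(p(1−p) × design effect / 400). To credit 14 of 26 units, the variance becomes p(1−p) × [(1 − 14/26) × ICC/14 + (1 − ICC)/400].

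| Assumed ICC | Design effect | Effective n | Half-width, p = 0.50 | Same, crediting 14 of 26 | Half-width, p = 0.20 | Same, crediting 14 of 26 |
|---|---|---|---|---|---|---|
| 0.02 | 1.55 | 258 | 6.1 | 5.5 | 4.9 | 4.4 |
| 0.05 | 2.38 | 168 | 7.6 | 6.2 | 6.0 | 4.97 |
| 0.10 | 3.76 | 106 | 9.5 | 7.3 | 7.6 | 5.8 |

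The credit is generous. It applies to sampling centres from a finite list, not to differences between testers, which would remain if all 26 units took part.

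**4. Coverage of an interval that ignores centre.** At p = 0.50 coverage is 2Φ(1.96 × 4.9 / true half-width) − 1. A nominal 95% interval would cover 88% / 80% / 69% for the three ICCs, or 92% / 88% / 81% with the 14-of-26 credit.

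**5. Lower prevalence.** Without any credit, the largest ICC that keeps 5 points is 0.009 at p = 0.30, 0.023 at p = 0.20 and 0.069 at p = 0.10.

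**6. Would more children help?** With 14 centres fixed and p = 0.50, 5 points would need about 835 children at ICC 0.02. The between-centre part of the variance, 0.25 × ICC/14, uses up the whole allowance (0.05/1.96)² at ICC = 0.036. Above that, no number of children in 14 centres reaches 5 points without the finite-population credit.

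**7. Few clusters.** The table uses 1.96, as the plan does. Fourteen clusters in two strata leave 14 − 2 = 12 degrees of freedom, where the t quantile is 2.18. That widens each half-width by about 11%: 6.1 becomes 6.8 and 7.6 becomes 8.4.

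**The case against.** The strongest reply is that nothing here is miscalculated and nothing is proved to fail. That stands as far as it goes. A reader might infer an arithmetic error in 384; there is none. A reader might also infer that the 5-point margin is certainly missed. The protocol does not support that: it contains no ICC, and p = 0.50 is the worst case for width. At 20% prevalence the half-width is 4.9 points with ICC 0.02, and 4.97 with ICC 0.05 if 14 of 26 units are credited. The only prevalence figures in Annex 3 (4.1 and 4.9, for severe retardation in two provinces) are a loose guide, but they point to lower values. Yet p = 0.50 was taken because the prevalence is unknown, so that the margin would hold whatever it turns out to be. That guarantee is what is lost.

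A second reply is that if the target is only children seen at the 14 units, those units are strata and centre sampling adds no variance. This is correct, but Annex 3 names the two zones, and tester differences remain. Training by a psychomotor therapist, the caregiver-completed questionnaire and software scoring may reduce those differences; by how much is unknown.

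Third, choosing busy, accessible centres is a matter of bias and generalisability, which a design effect cannot repair. This also stands, and the remedy has to say so.

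Fourth, Annex 3, 3.3.2 defines no interval for the prevalence, and such detail may sit in an analysis plan not shown. The absence of a centre term there is accordingly not the fault. The fault is that the protocol fixes a margin on an assumption that its own sampling scheme does not meet.

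Finally, a reader might extend the point to the comparison of arms. Randomisation is within each UNTA (sections 1.3 and 2.2.1), so centre and tester effects fall on both arms alike, and the comparison is not affected.

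**Conclusion.** The concern holds in this form: 384 is correctly computed and 400 is adequate under simple random sampling, but the 5-point margin for the prevalence in the two zones is not secured by the sampling described. At the plan's own p = 0.50, an ICC above about 0.0015 breaks it. For an assumed ICC of 0.02 to 0.05 the half-width is 6.1 to 7.6 points, or about 5.5 to 6.2 with the 14-of-26 credit; at ICC 0.10 it is 9.5, or 7.3 with the credit.

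These sizes rest on an assumed ICC, equal cluster sizes, p = 0.50, and the reading of one UNTA per health centre. At low prevalence the margin may still be met. The consequence is limited to the precision of one sub-study estimate and the population to which it applies. It is worth correcting because that estimate is the sub-study's first objective and the correction needs no extra children.

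**What to change.** 1. **Annex 3, 3.1.4.** Keep 400 children. State that 384 is the simple-random-sample figure, and give the expected 95% margin at p = 0.50 as about 5.5 to 8 points for an assumed ICC of 0.02 to 0.05. Say that this range uses 1.96 and runs from the case with the 14-of-26 credit to the case without it; with the t quantile below it is about 11% wider.
2. **Annex 3, 3.3.2.** Compute the prevalence interval with UNTA as cluster and health zone as stratum, using a t quantile on about 12 degrees of freedom.
3. **Annex 3, section 2 or 3.1.4.** State that the estimate applies to children admitted at the selected UNTAs. The clustered interval does not correct for the purposive choice of those units, so it should not be offered as an interval for the two zones as a whole.

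The cost is a few sentences and a standard survey command in the Stata software already planned, with no additional children or visits. The downside is that the stated margin becomes less favourable and the claim narrower.

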### 3.1.5. Sampling technique

This is a systematic study with a survey step of 2. In practice, after the first child, it is the 3rd child who will be the next participant according to the inclusion criteria until reaching the necessary 400. for this study.

## 3.2. Recruitment

Patients will be recruited at the UNTA level whether they come directly from the community or whether they are referred from the CPS.

The participants will be distributed among the different UNTAs in proportion to the demographic weight.

On admission, anthropometric measurements including weight, height, MUAC, head circumference and nutritional edema will be taken on all children. To be recruited, each participant must have one must meet the inclusion criteria of the under study. Individuals with

SAM but who do not meet the criteria for the sub-study will be included in the parent study or managed according to the PCIMA protocol but will not be part of the sample for this study if applicable.

